### Intervention

The treatment period is set at four months and consists of either the physical exercise training programme or the sham-treatment. The intervention will be carried out by physiotherapists working in a primary care setting, with broad expertise and education in COPD. The treatment protocol is standardised, the Dutch Guideline Physiotherapy in COPD serves as a framework, and based on individual problems and possibilities of the patient [41].

#### Intervention group (Physical Exercise Training Programme)

The physical exercise training programme has four main goals; improvement in exercise capacity, muscle strength, daily physical activity and breathing technique. The physical training component entails endurance training and/or interval training [41]. Walking speed on the treadmill is executed with an intensity of 75% or higher of the results of the six-minute walk test (6MWT). Ratings of perceived exertion and dyspnoea of five and higher on the modified Borg-scale (0–10) are used to tailor exercise intensity [42].

Resistance training in addition to endurance or interval training is recommended in all patients, especially important in patients with peripheral muscle weakness. In the absence of any comparative studies it is recommended to use both upper limb and lower limb resistance weight training at an intensity of at least 60-80% of the one repetition maximum, 2 to 3 sets of 8–12 repetitions are preferable [41].

Much emphasis is given to the assessment and treatment of physical inactivity in daily life. Patients are advised to increase their total physical activity. Patient and physiotherapist together define a strategy to meet the ACSM-recommendation for physical activity, i.e. performing moderately intense physical activity for 30 minutes on at least five days a week [33].

Breathing exercise is an embracing term for a range of exercises such as active expiration, slow and deep breathing, pursed lips breathing, relaxation therapy, body positions such as forward leaning and diaphragmatic breathing [41].

The physical exercise training programme will consist of two supervised sessions per week in the physiotherapy setting in primary care. These sessions will be with 1–5 patients at the time and the duration of each session will be 60–90 minutes, depending on group size. From an organisational and practical point of view it is not feasible to ask patients to come to a physical therapy setting more often. Furthermore, as mentioned before, an important part of the programme is enhancement of daily physical activity. So, patients are requested to perform an additional training session at home, including walking and/or cycling and they have to report these activities weekly to the physiotherapist. It is our aim to enhance the awareness and responsibility of our patients to change their physical activity behaviour for the long term and this encompasses enhancement of self-management and self-efficacy.

#### Control group (sham-treatment)

According to the national guidelines of the Dutch College of General Practitioners (NHG) and the Multidisciplinary Guideline on non-pharmacological treatment of COPD, the GP and the nurse practitioner should give advice to improve the physical condition [5, 43]. Verbal advice will be supported by a written brochure. This brochure is developed in collaboration with the NHG as part of a preceding implementation project of physiotherapy for COPD patients in primary care [44].

In addition, the patients in the control group will participate in a sham-treatment at the physiotherapy practice. This treatment consists of 30 minutes once a week “exercise” training, with ratings of perceived exertion and dyspnoea of 2 or lower on a modified Borg-scale. It is unlikely that a physiologic training stimulus will occur at these levels of exertion. There will be no breathing exercises or resistance training. Furthermore, patients will be advised to do at least 30 minutes of moderate intense physical activities on at least five days a week according to the ACSM-recommendation for physical activity [33].

### Outcome measures

All outcomes will be assessed at baseline (T0), at the end of intervention after four months (T1) and at the end of follow-up (T2) at six months.

#### Primary outcome measure

The primary outcome measure will be the functional exercise capacity measured by the increase in the six-minute walk distance (6MWD) at 4 months compared to baseline. The six-minute walk test (6MWT) will be performed in accordance with the ATS Statement: guidelines for the 6MWT [45], except that a standard 30-meter corridor will not always be feasible in a primary care physiotherapy practice, but the minimal track will be 10 meter. The results will be expressed in absolute values and as percent of the predicted value [46]. During the walk test, perceived fatigue and dyspnoea will be measured on a modified Borg scale ranging from zero (nothing at all) to ten (very, very severe) [47]. Oxygen saturation and pulse rate will be measured by a finger pulse oximeter (Onyx 9500) [45].

#### Secondary outcome measures

Isometric handgrip force will be measured with a hydraulic handheld dynamometer (Yamar Preston, Jackson MI). Peak handgrip force (in Newton) will be assessed at the dominant side with the elbow at 90 degrees flexion, with the underarm and wrist in neutral position [48]. Isometric knee extension and shoulder abduction force will be measured in standardised positions by a handheld dynamometer by means of the break method [42, 49]. Peak torques will be measured at the dominant side according to Andrews et al. [49]. At least three attempts will be performed for all muscle tests.

Self-reported daily physical activity will be assessed by the brief physical activity assessment tool [50]. Objective daily physical activity will be measured during 3 consecutive days and nights with an accelerometer-based activity monitor (Dynaport; McRoberts BV). Data of both intensity of movement and duration will be collected, like steps per day, total active time per day, time spent in moderate intense physical activities and vigorous activities and physical activity level (PAL). All patients will be carefully instructed on how the activity monitor should be positioned and they will receive a manual with clear instructions and figures. They will also have to fill out a checklist to verify if their day was a representative one and to indicate any possible hindrance of the activity monitor.

The level of dyspnoea will be assessed by the Medical Research Council (MRC) dyspnoea score [51]. Specific Health Related Quality of Life (HRQL) will be assessed by means of the Clinical COPD Questionnaire (CCQ) [52, 53] and the Chronic Respiratory Questionnaire (CRQ-SR) [54–56]. The global perceived effect (GPE) of the treatment according to the patients will be measured on a GPE scale [57, 58].

Furthermore, the following baseline characteristics will be measured, height, weight, Body Mass Index (BMI) and level of motivation by means of the questionnaire (Dutch translation) according to Miller and Rollnick et al. [59–61].

### Data analysis

The descriptive characteristics will be presented quantitatively as means (±standard deviation) for continuous variables and as medians for categorical variables and will be presented for the total group, as well as for the separate groups. Unpaired t-tests will be used to compare the effects of the treatment between the intervention group and control group at the end of the physical exercise training programme (4 months). P-values smaller than 0.05 will be considered as statistically significant.

Group (intervention vs. control) by time (pretest vs. posttests) repeated measurements analysis of variance (RM ANOVA) will be performed to examine (1) intervention main effect, (2) time main effect, and (3) intervention by time interaction effect on each of the continuous primary and secondary outcomes. An analysis of covariance will be done to evaluate the relationship between covariates and the dependent variable. The random effect will also be evaluated, since participants from both arms will be nested within the same physiotherapy setting. To evaluate which factors predict a positive outcome, i.e. the physical exercise training programme is effective, a multiple linear regression analysis will be done, using interaction terms between predictors and physical exercise. A predictor variable will make a significant contribution to predicting the outcome when P-value is smaller than 0.05. The following possible predictors are taken into account, baseline: MRC dyspnoea score, walking distance, peripheral muscle strength, level of daily physical activities and compliance with the training programme [62–64].

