### Objectives

The primary objective of our study is to evaluate the *efficacy* of a physical exercise training programme (PETP) in patients with mild to moderate COPD in the primary care setting on exercise capacity, physical activity, dyspnoea and quality of life. The 6 month time point is aimed at gaining more insight into the lasting of the effects.

The secondary objective is to assess how patient characteristics and baseline burden of disease modify the effect of a physical exercise training programme on functional exercise capacity in patients with mild to moderate COPD in primary care.

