### Sample size calculation

We performed a pilot study in one physiotherapy setting in order to get a rough idea of the improvement in six-minute walk distance (6MWD) in this group of patients after a 4-month physical exercise training programme. Data of six patients with mild to moderate COPD were collected. Their mean 6MWD was 475 metres with a standard deviation of 62. These patients increased their 6MWD by a mean of 52 metres. Troosters et al. reported a mean difference in change from baseline of 52 metres between the intervention group and control group, in a study of the short- and longer-term benefits of 6 months pulmonary rehabilitation [35]. A more recent study showed an improvement of 54 metres with a standard deviation of 78 metres after a 7 week pulmonary rehabilitation programme [11]. Our assumptions for this study are that the mean difference in change from baseline between the intervention group and the control group (δ) is 52 metres (52–0 m), with a standard deviation (σ) of 78 metres [11]. According to the effect size measures for two independent groups this implies a large effect size (Cohen’s d = δ/σ = 52/78 = 0.66) [36]. The sample size needs to be 36 patients per treatment arm (72 in total), whereby α = 0.05 (2 tailed), 80% power and a ratio of control to experimental patients of 1:1. This sample size calculation is done by using the PS power and sample size program of Dupont and Plummer [37, 38].

A total patient number of 102 participants (51 per treatment arm) is needed, based on the abovementioned calculation and allowing for dropouts (30%). Previous studies showed a drop-out rate varying from 26 to 31% [11, 35, 39, 40].

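### The 4-month 6MWD comparison is a valid unpaired t-test that does not use baseline 6MWD as a covariate, and no test is named as decisive

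*Protocol article*

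**What the plan says.** All in the protocol article.

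- **Primary outcome measure** defines the outcome as "the increase in the six-minute walk distance (6MWD) at 4 months compared to baseline".
- **Sample size calculation** works on the same scale: a between-arm difference in change of 52 m with an SD of 78 m, "whereby α = 0.05 (2 tailed), 80% power and a ratio of control to experimental patients of 1:1". The result is 36 per arm. The only cross-sectional SD comes from six pilot patients: "Their mean 6MWD was 475 metres with a standard deviation of 62".
- **Bias, confounders and limitations** confirms that difference scores, 4 or 6 months minus baseline, are what the authors want to compare.
- **Data analysis** first gives the comparison at the end of the 4-month programme: "Unpaired t-tests will be used to compare the effects of the treatment between the intervention group and control group at the end" of the programme, followed by the 0.05 threshold. It then plans a group-by-time repeated-measures ANOVA, with a group main effect, a time main effect and an interaction, for every continuous primary and secondary outcome. Next comes ANCOVA: "An analysis of covariance will be done to evaluate the relationship between covariates and the dependent variable". Because both arms are treated within the same practices, a random effect will be evaluated. Baseline walking distance is named only among the candidate predictors in the effect-modification regression.

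**The concern.** Three features of the Data analysis section matter.

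1. Baseline 6MWD is collected from everyone and should predict the 4-month value, yet it is not a covariate in the treatment comparison. Subtracting baseline forces its coefficient to be 1. ANCOVA estimates the coefficient, and with equal variances at both visits it is more precise at any correlation below 1. It also corrects for chance baseline imbalance, which can occur with about 72 completers.
2. Practice is recognised as a source of structure, and walking tracks differ between practices, but the practice effect is not tied to the primary comparison.
3. The t-test, the ANOVA group effect and the ANOVA interaction all compare the arms on 6MWD, and they answer different questions. The t-test concerns 4 months. The interaction also draws on 6 months if all three visits enter. The group effect averages in the pre-treatment visit and so dilutes any benefit. If they disagree, the text does not say which one settles the trial.

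At stake are precision that costs nothing to recover and a clear rule for the main claim.

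**Working it through.** **Inputs from the article:** difference 52 m; SD of change 78 m; two-sided alpha 0.05; power 80%; 36 per arm; pilot SD 62 m; visits at 0, 4 and 6 months. **Not in the article:** the correlation r between baseline and 4-month 6MWD. It is assumed to be 0.5 to 0.9, with equal variances at the two visits.

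**Step 1: the plan's own figure.** n per arm = 2 × (1.960 + 0.842)² × (78/52)² = 35.3, rounded up to 36. This reproduces. Noncentral-t power at 36 per arm with d = 52/78 is 79.7% (80.7% by the normal approximation).

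**Step 2: ANCOVA against the change-score t-test.** With common visit variance σ², the change score has variance 2σ²(1−r) and the ANCOVA residual has σ²(1−r²). The ratio is (1−r²)/[2(1−r)] = (1+r)/2. Holding the change SD at 78 m, the equivalent ANCOVA SD is 78 × √[(1+r)/2].

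| assumed r | variance ratio | equivalent SD (m) | power, 36 per arm | n per arm for 80% (normal) |
|---|---|---|---|---|
| t-test on change | 1 | 78.0 | 79.7% | 36 |
| 0.5 | 0.75 | 67.5 | 89.6% | 27 |
| 0.7 | 0.85 | 71.9 | 85.7% | 31 |
| 0.8 | 0.90 | 74.0 | 83.7% | 32 |
| 0.9 | 0.95 | 76.0 | 81.6% | 34 |

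The variance ratio depends only on r. The power column also depends on fixing the change SD at 78 m, which implies a cross-sectional SD of 78/√[2(1−r)]: 78 m at r = 0.5, but 174 m at r = 0.9.

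**Step 3: if the t-test were run on raw 4-month values.** The ratio of ANCOVA variance to t-test variance would be 1−r²: 0.75, 0.51, 0.36 and 0.19 at r = 0.5, 0.7, 0.8 and 0.9. The loss would then be largest where the change-score loss is smallest.

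**Step 4: several tests on 6MWD.** Null trials were simulated (36 per arm, three visits, r from 0.21 to 0.9, constant or decaying correlation, 100,000 trials per setting). The chance that at least one of three tests (t-test, ANOVA group effect, ANOVA interaction) has P < 0.05 was:

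- 12.0% to 12.5% with the t-test on change;
- 11.0% to 12.2% with the t-test on raw 4-month values.

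For comparison, three independent tests would give 1 − 0.95³ = 14.3%. If the ANOVA used only baseline and 4 months, its interaction would be the same test as the change-score t-test, and the figure would be 1 − 0.95² = 9.75%. The t-test alone gives 5%.

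**The case against.** The strongest reply is that nothing here is invalid. In a randomised trial the change-score t-test is unbiased and holds 5%. It matches the sample size calculation, which reproduces, so the trial is not underpowered on its own assumptions. That stands: the loss is one of efficiency.

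Several stronger readings are tempting and are not supported.

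- *Baseline is ignored.* Three sections point to a change score, so baseline is subtracted. What is missing is its use as a covariate.
- *The trial has a 12% false-positive rate.* That needs a rule that any significant test counts as success, and the article states none. The t-test comes first and is the only analysis tied to 4 months, so a reader can reasonably take it as primary. The article simply does not say so.
- *ANCOVA would lift power to 95%.* That comes from r = 1 − 78²/(2 × 62²) = 0.21, which combines an SD from six pilot patients with a change SD from a different 7-week programme. It is not an estimate of the correlation. Conversely, if the SD of 62 m held with r of 0.7 or more, the change SD would be at most 48 m and power would exceed 99% by either method.
- *There are several primary outcomes.* The Objectives section does list effects "on exercise capacity, physical activity, dyspnoea and quality of life", but the abstract and the outcome sections make 6MWD the only primary outcome.
- *Leaving practice out invalidates the t-test.* Patients are randomised individually and both arms are expected in each practice. With additive practice effects, omitting practice tends to be conservative.

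It may also be said that covariate lists belong in a fuller analysis plan. That is fair for the list. But the article itself chooses the t-test for the comparison and gives ANCOVA another purpose, so the point rests on what is stated.

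**Conclusion.** The point holds as a loss of efficiency together with an unnamed deciding test. Against a change-score t-test, the baseline-adjusted model would remove 25% of the variance at r = 0.5, falling to 5% at r = 0.9. At 36 per arm with a change SD of 78 m, power is about 90% to 82% instead of 79.7%. These figures assume equal variances at both visits and a correlation that the documents do not give; at high correlation the gain is modest. The false-positive figure of up to about 12% is conditional on allowing any of the three tests to carry the claim. It describes what the open wording would permit, not the error rate of the plan.

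**What to change.** In Data analysis, state one primary analysis: 4-month 6MWD in metres, regressed on allocated arm and baseline 6MWD, with physiotherapy practice in the model as a random or fixed effect. Report the adjusted difference with its 95% confidence interval and a two-sided P value at 0.05. Label the unpaired t-test and the repeated-measures ANOVA results as supportive. The sample size can stay as it is, because 36 per arm is sufficient for the less efficient test.

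The cost is a few sentences. No further patients, visits or measurements are needed.

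### The RM ANOVA group main effect averages over the pretest and so is not a treatment effect, and no named analysis answers the 6-month durability aim

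*Protocol article*

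**What the plan says.** Under Data analysis, the protocol article first plans unpaired t-tests between the arms at the end of the programme (4 months). It then adds a repeated-measures ANOVA with factors "Group (intervention vs. control) by time (pretest vs. posttests"). For every continuous primary and secondary outcome, this "RM ANOVA) will be performed to examine (1) intervention main effect, (2) time main effect, and (3) intervention by time interaction effect". The section does not say which of these results carries the conclusion. It also plans an analysis of covariance to relate covariates to the outcome, and an evaluation of a random effect because patients of both arms are nested in the same physiotherapy setting.

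Other sections fix the context:

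- Outcome measures: every outcome is taken at baseline (T0), 4 months (T1) and 6 months (T2).
- Study design: the intake measurement precedes treatment and is its starting point.
- Primary outcome measure: the increase in 6MWD from baseline to 4 months.
- Objectives: "The 6 month time point is aimed at gaining more insight into the lasting of the effects".
- Bias, confounders and limitations: interest lies in difference scores, 4 or 6 months minus baseline.

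**The concern.** A group main effect in a group-by-time ANOVA is the arm difference averaged over all levels of time. Here one of the three levels is measured before treatment. The expected difference there is zero, and whatever difference chance produces enters the average as if treatment had caused it. Read as a treatment effect, the result is too small by construction and mixes in baseline imbalance.

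The interaction term is free of the first problem but has 2 degrees of freedom. A significant result says that the arm difference is not constant over T0, T1 and T2. It does not say where the arms differ.

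The t-tests are confined to 4 months, so the 6-month data enter only through the RM ANOVA, and none of its three listed effects is the 6-month difference. A report that followed the text literally could give a diluted effect for each continuous outcome and leave the durability question without a matching estimate.

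**Working it through.** **Inputs from the Sample size calculation section.**

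- Evaluable patients: 36 per arm, 72 in all.
- Effect: the arms are assumed to differ by 52 m in their change from baseline.
- Spread: σ = 78 m, taken as the SD of that change.
- Error rates and allocation: "whereby α = 0.05 (2 tailed), 80% power and a ratio of control to experimental patients of 1:1".
- Cross-sectional SD of 6MWD: the only one given is 62 m, from a pilot of six patients.

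**The plan's own figure.** n per arm = 2(1.960 + 0.842)² × (78/52)² = 2 × 7.85 × 2.25 = 35.3, rounded up to 36. It reproduces. With the t distribution, power at 36 per arm is 79.7%. The sample size therefore belongs to the 4-month difference in change, not to the RM ANOVA main effect.

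**What the main effect estimates.** With complete data the three visits have equal weight:

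main effect = (0 + d4 + d6)/3

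mean posttest effect = (d4 + d6)/2

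ratio = 2/3, whatever d4 and d6 are.

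With d4 = 52 m:

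| d6 (m) | Mean posttest effect (m) | Main effect (m) | Below the 4-month effect |
|---|---|---|---|
| 0 | 26.0 | 17.3 | 67% |
| 26 | 39.0 | 26.0 | 50% |
| 52 | 52.0 | 34.7 | 33% |
| 60 | 56.0 | 37.3 | 28% |
| 78 | 65.0 | 43.3 | 17% |

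**Baseline imbalance.** Under compound symmetry with correlation r between visits, an observed baseline difference D shifts the main effect by D(1 + 2r)/3. One standard error of D is SD × √(2/36).

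- SD 62, r = 0.21: 14.6 × 0.473 = about 7 m.
- SD 78, r = 0.5: 18.4 × 0.667 = about 12 m.

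**What the interaction shows.** With error variance 78²/2 = 3042, the noncentrality is λ = (36/2) × Σ(g − ḡ)²/3042, on 2 and 140 df. For arm differences 0/52/52 m at T0/T1/T2, the sum of squares is 1803 and λ = 10.7, which gives 83% power. The patterns 0/52/0 and 0/0/52 have the same sum of squares and so the same 83%. A lasting effect, one that has vanished by 6 months and one that appears only at 6 months are equally likely to give a significant interaction.

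**Power of the main-effect test.** The correlation r is not documented, so a range is shown. A change SD of 78 implies a cross-sectional SD σ = 78/√(2(1 − r)), and the three-visit mean has SD σ√((1 + 2r)/3). Noncentral t, 36 per arm:

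| r (assumed) | σ (m) | SD of mean (m) | Power, d6 = 52 | Power, d6 = 26 |
|---|---|---|---|---|
| 0.21 | 62 | 42.7 | 92% | 72% |
| 0.5 | 78 | 63.7 | 62% | 40% |
| 0.8 | 123 | 114.8 | 24% | 16% |

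The comparison is 79.7% for the 4-month change. The main effect is more powerful than the t-test at the pilot SD for a sustained effect, and less powerful in every other cell.

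**The case against.** The strongest reply is that the primary question is already covered. The primary outcome is the 4-month change, the t-test compares the arms at 4 months, and the sample size matches a comparison of changes. This stands. A reader might infer that the RM ANOVA undermines the primary comparison; the protocol does not support that.

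A second reply is that the main effect is only one of three terms to be examined, which is routine output, and nothing names it as the efficacy estimate. This is also fair and lowers the severity. But it is listed as the intervention effect for every continuous outcome, with no order among the results, so the misreading is open.

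Third, the limitations text names the 6-month difference score as of interest, and follow-up contrasts are often left to a fuller document. The stated interest is real, so it would be wrong to say that the authors overlooked month 6. The point is narrower: the article does state how month 6 enters the analysis, and the terms it lists do not give that difference. If the model held only T0 and one posttest, the interaction would equal the t-test on change. The plural posttests and the three assessments make the three-level reading the natural one.

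Fourth, a reader might infer that the trial loses power. That is not established. It depends on a correlation the protocol does not give, and at the only documented SD the main effect has about 92% power for a sustained 52 m.

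**Conclusion.** The concern holds in a limited form. The RM ANOVA main effect over pretest and posttests should not be read as a treatment effect. With equal visit weights and no effect at T0, it is exactly one third below the mean posttest effect: 34.7 m for a sustained 52 m, 26 m if the effect halves by 6 months. The omnibus interaction cannot separate 4 months from 6 months, so the Data analysis section names nothing that answers the durability aim.

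Two limits apply. It is tempting to say that the main effect is at least a third below the 4-month effect, but that needs a 6-month effect no larger than the 4-month one. This is plausible once training stops, but the protocol does not state it. The baseline-imbalance and power figures assume compound symmetry, and the power range is too wide to support a claim of lost power.

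Severity is moderate: the primary 4-month 6MWD comparison stands on its own t-test.

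**What to change.** Drop the main effect over pretest and posttests as a treatment effect. Analyse T1 and T2 as outcomes with the baseline value as covariate and arm-by-visit terms, for example in a linear mixed model that also holds the practice random effect already intended. Report the arm difference with 95% CI at 4 months (primary) and at 6 months, and state that the 4-month difference carries the conclusion.

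A mixed model is one way to do this. The essential changes are the two visit-specific differences and the stated order between them.

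The cost is analysis wording only: no new data, visits or patients. The 6-month estimate will be imprecise. If the SD of change is also 78 m there, an unadjusted 6-month contrast with 36 per arm has 79.7% power for 52 m but only 28.6% for 26 m. It should therefore be reported as an estimate with its interval, and a non-significant result should not be read as loss of the effect.

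### Compliance with the training programme is listed as a treatment-effect modifier, although it arises after randomisation and controls do not receive that programme

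*Protocol article*

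**What the plan says.** The secondary objective (Objectives) is to assess "how patient characteristics and baseline burden of disease modify the effect of a physical exercise training programme" on functional exercise capacity. The matching analysis (Data analysis) states that "a multiple linear regression analysis will be done, using interaction terms between predictors and physical exercise". The predictors are then listed: "The following possible predictors are taken into account, baseline: MRC dyspnoea score, walking distance", followed by peripheral muscle strength, "level of daily physical activities and compliance with the training programme". Each is judged on its own P-value against 0.05.

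The sections on the two arms describe different activities. The intervention arm has two supervised sessions a week of 60 to 90 minutes, plus a session at home that the patient reports weekly to the physiotherapist. The control arm has one 30-minute sham session a week at Borg 2 or lower, and "There will be no breathing exercises or resistance training". Under Bias, confounders and limitations, controls may be offered the training programme only after the study period, and only if it has proved efficacious. Randomisation follows consent (Randomization and blinding), so all compliance is recorded after allocation.

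**The concern.** An effect modifier in a randomised comparison should be a variable that exists in both arms and is fixed before allocation. The interaction then compares like with like: the treatment effect at one level of the variable against the effect at another. Compliance with the training programme meets neither condition, and it lies outside the stated secondary objective.

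The practical risk is in the interpretation. A significant compliance term would be read as evidence that the programme works better in those who adhere to it. The same result would appear if patients who were going to do well anyway simply attended more. The design leaves room for such a link: home sessions are reported to the physiotherapist, who is unblinded, delivers the treatment and also takes the measurements. In a joint model, an uncentred compliance interaction also turns the arm coefficient into the effect at zero compliance.

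**Working it through.** **Inputs.** From Sample size calculation: difference 52 m, SD 78 m, 36 completers per arm (72 in total), two-sided 0.05, 80% power, 30% dropout. The documents give no correlation between compliance and walk gain, so every correlation below is an assumption.

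**The plan's own figure.** n per arm = 2 × (1.96 + 0.84)² × 78² / 52² = 2 × 7.84 × 2.25 = 35.3, rounded up to 36. Dividing 72 by 0.7 gives 102.9, against 102 stated. This agrees within rounding and is not in dispute. The plan gives no figure for the interaction analysis.

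**Coding 1: controls set to zero.** The model has an intercept, arm, compliance and arm × compliance. Compliance is zero whenever arm is zero, so compliance and arm × compliance are the same column. The design matrix has rank 3 for 4 columns (checked numerically). If one of the two columns is dropped, the remaining coefficient is the slope of gain on compliance within the intervention arm; controls contribute nothing to it. If there is no true modification, a correlation r between compliance and gain in that arm gives an expected slope of r × 78 m per SD of compliance. Simulation (72 completers, 4,000 replicates, constant 52 m effect) gave:

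| Assumed r | Expected slope r × 78 | Simulated slope | Declared significant |
|---|---|---|---|
| 0 | 0 m | -0.1 m | 4% |
| 0.15 | 11.7 m | 11.9 m | 14% |
| 0.25 | 19.5 m | 19.5 m | 31% |
| 0.35 | 27.3 m | 27.0 m | 55% |

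(The simulation let a latent prognosis explain 25% of outcome variance, so r is half the compliance-prognosis correlation of 0, 0.3, 0.5 or 0.7.)

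**Coding 2: compliance missing in controls.** The interaction has no control data and cannot be fitted.

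**Coding 3: sham attendance used for controls.** The term is estimable. Per SD of attendance, each arm's slope has standard error 78/√36 = 13.0 m, so their difference has standard error 2 × 78/√72 = 18.4 m. With no true modification, the expected interaction is (r in training arm − r in sham arm) × 78 m, and the rejection rate is P(|Z + interaction/18.4| > 1.96):

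| r training vs r sham | Spurious interaction | Ratio to SE | Declared significant |
|---|---|---|---|
| 0.3 vs 0.3 | 0 m | 0 | 5% |
| 0.3 vs 0.2 | 7.8 m | 0.42 | 7% |
| 0.1 vs 0 | 7.8 m | 0.42 | 7% |
| 0.3 vs 0.1 | 15.6 m | 0.85 | 14% |
| 0.3 vs 0 | 23.4 m | 1.27 | 25% |
| 0.5 vs 0 | 39.0 m | 2.12 | 56% |

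The last row rises to about 62% if the residual SD is reduced for the variance that compliance explains; the other rows move by about one percentage point or less.

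**The case against.** Several points on the other side stand.

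- Controls do attend weekly, so an attendance variable can be built for both arms. If attendance relates to prognosis equally in both, the interaction is unbiased. A reader might infer that the term must be either non-estimable or biased. The documents do not support that: bias is a risk of unknown size.
- If patients who would improve anyway attend more, the same may hold for sham sessions. The 0.3 versus 0 case is therefore one scenario, and its 25% should not be quoted alone.
- With zero coding, the coefficient that survives is a legitimate within-arm description. What is wrong is calling it an interaction and reading it causally.
- The word baseline may be meant to govern only the first four predictors, with compliance appended. This softens the labelling complaint. It does not rescue the term, because the plan's phrase "using interaction terms between predictors and physical exercise" covers every predictor on the list.

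Two wider inferences also go too far. A reader might extend the point to the main result, but the 4-month comparison is a separate unpaired t-test and does not use this model. A reader might also fold in the rule that "A predictor variable will make a significant contribution to predicting the outcome when P-value is smaller than 0.05", and the low power of interaction tests. Those are separate matters from compliance, and handling of multiplicity in a secondary predictor search is something an article may leave to an analysis plan that is not shown.

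Leaving details to such a plan does not answer the main point. The article itself names compliance as a term to be interacted with treatment, and none of the three codings above gives that term a valid reading as an effect modifier without an equal-prognosis assumption that randomisation does not guarantee.

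**Conclusion.** The point holds for one of the five listed predictors, in the analysis that serves the secondary objective. As written, the compliance interaction cannot validly show who benefits from the programme. It is inseparable from the main effect under zero coding, and under sham-attendance coding it mixes adherence to two different activities. The false-positive rate could lie anywhere from the nominal 5% (equal correlations) through 14% and 25% to above 50% (strong asymmetry). These figures rest on 72 completers, SD 78 m, no true modification and correlations that the documents do not supply. The primary 4-month comparison and the sample size are unchanged.

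**What to change.** In Data analysis, restrict the treatment-interaction model to the four baseline predictors: MRC dyspnoea score, walking distance, peripheral muscle strength and level of daily physical activity. Remove compliance from that list, so that the baseline label is correct and the model matches the secondary objective. Add a sentence that the association between compliance and walk gain will be reported separately within the intervention arm, labelled descriptive and non-causal.

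The cost is a change of wording and the loss of a P-value for compliance as an effect modifier. No extra data or patients are needed. Replacing compliance with baseline motivation, or adding a complier-average analysis, is optional: motivation is a different construct, and a complier-average effect needs a definition of a complier and an exclusion restriction that is doubtful with unblinded patients who may benefit from partial attendance.
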